## **9.2 Assessment and Documentation of Adverse Events**

For the purposes of this study the investigator is responsible for recording all Adverse Events, regardless of their relationship to the study intervention, with the following exceptions:

- Conditions that are present at screening and do not deteriorate will not be considered adverse events.

The description of each AE on the study database will include:

- A description of the AE;
- The onset date, duration, date of resolution;
- Severity (mild, moderate or severe);
- Seriousness (i.e. is it an SAE?);
- Any action taken, (e.g. treatment, follow-up tests);
- The outcome (recovery, death, continuing, worsening);
- The likelihood of the relationship of the AE to the study treatment (Unrelated, Possible, Probable, Definite).

The seriousness of an AE will be assessed by an investigator according to the definition in section 9.1, with the following exception:

- Hospitalisation due to progression of disease will not be considered an SAE for the purposes of this study.

For the right@home study, the most likely AEs/SAEs that nurses and researchers will encounter are psychosocial, substance abuse, home safety and child protection issues (e.g. abuse, neglect). Where an incident that requires a child protection notification occurs during a nurse visit, the nurses will respond in accordance with their local mandatory reporter guidelines. This is part of usual care, and thus involves no change in practice for the nurses. The baseline PIS&C (Appendix 2) includes the following: “We can disclose the information only with your permission, unless required by law”, which alerts the participant to the need to remain within the law.

Where the incident occurs during a researcher visit, we will follow the processes used successfully in MECSH. For psychosocial and drug/alcohol problems, researchers will recommend that women phone the maternal and child health line ([name]). They will also ask if the woman would like CI [name] to phone and offer a more specific referral. For domestic violence and child abuse/neglect problems, researchers will report using the local public child protection system, i.e. via the usual public child protection helpline ([name]). Researchers with concerns will be asked to discuss, in the first instance, the child protection issue with CI [name] (see details in the Safety and Communication Protocol, Appendix 21). While researchers are not mandatory reporters, CI [name] is. The research team will follow-up as required based on the response from the child protection system. The research staff will also be provided with support and debriefing from CIs and MCRI counselling.

Changes in the severity of an AE will be reported. AEs characterized as intermittent will be documented for each episode. All AEs will be followed to adequate resolution, where possible.

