### 6.2.1 Inclusion Criteria

Vulnerable, pregnant Australian women, who have sufficient English proficiency to answer questions face-to-face. The inclusion criteria, based on the results of our pilot (RCH HREC 32771, Northern Health HREC P 20/12), are any two of the following 10 risk factors:

- Current smoking,
- Young pregnancy (<23 years old),
- No support (emotional, financial, practical) during pregnancy,
- Poor/fair/good general health (versus very good/excellent general health)
- Anxious mood,
- Not finishing high school,
- Not having a household income,
- A long-term illness,
- Living without another adult, and
- Never had a job.

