#### **Serious Adverse Event (SAE)**

An SAE is defined as any AE that:

- results in death; or
- is immediately life threatening; or
- requires inpatient hospitalisation; or
- requires prolongation of existing hospitalisation; or
- results in persistent or significant disability/incapacity; or
- is a congenital anomaly/birth defect.

Important medical events will be considered an SAE when, based upon appropriate medical judgement, they may jeopardize the patient and may require medical or surgical intervention to prevent one of the outcomes listed in this definition.

We recognise that participation in the right@home study may be a cause of potential stress or harm to participants, if it asks questions that are distressing, or if participation leads to disagreements or fights between the participant and her partner and/or family. Potential stress will be minimised in the following ways:

1. The participant will be fully aware of the reason for the questions asked in the assessments
2. The participant will be advised that they can decline to continue in the trial at any time
3. Participants will be offered appropriate referral for any concerns raised

At recruitment screening, any women who becomes distressed will be encouraged to discuss their concerns with the health provider they are about to see. During the study if a research assistant is

concerned about a parent they will discuss this with the PI. With the parent's permission a referral mechanism will be in place to the parent's local doctor or maternal and child health nurse. This process has been implemented successfully with a number of other studies that specifically ask about self harm behaviour. If the parent is within the intervention arm the PI will contact the parent and ask permission to refer back to the intervention nurse.

At the 6 week, 6 month and 18 month follow-up phone assessments, women will be asked what things they like and dislike about being part of the study, and whether being part of the study has caused them any harm so far. These questions will be developed based on previous MCRI studies that have successfully used these processes (e.g. Weave Study, Healthy Mothers Study) and submitted for approval in a future ethics modification.

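### Section 9.2 exempts admissions for progression of an undefined disease from SAE status, so some admissions for worsening baseline conditions can miss the expedited HREC report

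*Protocol*

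**What the plan says.** **Seriousness.** Section 9.1 lists the criteria that make an adverse event serious, among them that it "requires inpatient hospitalisation; or". A further route is medical judgement: "Important medical events will be considered an SAE when, based upon appropriate medical judgement", followed by conditions on jeopardy to the participant and the need for intervention.

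**The exception.** Section 9.2 has an investigator judge seriousness by that definition, with one exception: "Hospitalisation due to progression of disease will not be considered an SAE for the purposes of this study". Neither 9.1 nor 9.2 defines the disease.

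**Recording.** Under section 9.2, "the investigator is responsible for recording all Adverse Events, regardless of their relationship to the study intervention". Baseline conditions are left out only while they are stable: "Conditions that are present at screening and do not deteriorate will not be considered adverse events".

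**Expected events.** After the exception, section 9.2 says that "the most likely AEs/SAEs that nurses and researchers will encounter are psychosocial, substance abuse, home safety and child protection issues".

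**Consequence of SAE status.** Section 9.4.1 sends every SAE to the RCH HREC within 24-72 hours.

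**Who is enrolled.** Section 6.2.1 admits women with any two of ten risk factors. Anxious mood and a long-term illness are two of the ten.

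**The concern.** An exemption for disease progression makes sense where a trial studies a disease whose natural course is expected and is captured elsewhere, for example as an outcome. This trial has no such disease. The conditions left for the clause to act on are those the women bring with them, and some of these are reasons for enrolment.

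At stake is safety oversight. Section 9.1 accepts that taking part may itself cause stress or harm. An admission for deteriorating mental health is therefore one that an ethics committee would want to see quickly, whatever its cause turns out to be. The protocol plans no interim analyses (section 10.4) and foresees no circumstances for early termination (section 6.7), so the expedited HREC report carries much of the weight. An undefined term also lets two investigators classify the same admission differently.

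**Working it through.** The protocol gives no figure on this point, so the check sets the sections against each other.

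**1. Does the exempted disease have a referent?** Sections 2.1 and 4.1 describe a comparison of home visiting with usual care, with parenting and home-environment outcomes. Section 6.2.1 defines the population by risk factors, not by a diagnosis. There is no index disease.

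**2. What can the clause act on?** Three of the ten entry factors concern health: general health, anxious mood and long-term illness. The first is a rating that counts even good health as a risk factor, so it is not a disease that can progress. Anxious mood and long-term illness remain. The other seven (smoking, age, support, education, income, living situation, work history) are not health states, and a woman can qualify on those alone.

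**3. Trace one admission.** Take a woman enrolled with anxious mood who is later admitted because it has worsened.
- Is it an adverse event? Yes: the condition was present at screening but has deteriorated, so the stable-condition exclusion in 9.2 does not apply.
- Is it serious under 9.1? Yes: it required inpatient admission.
- Is it serious after the exception in 9.2? Not if the investigator reads the worsening as progression of disease. The text neither requires nor rules out that reading.
- What follows if it is exempted? The event stays in the database with severity, action taken, outcome and relationship to the intervention. The 24-72 hour report to the HREC is no longer required.

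**4. Go through the four risk categories that 9.2 names.**

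| Named category | Can an admission be read as disease progression? | SAE status |
|---|---|---|
| Psychosocial | Yes, where a baseline condition worsens | Can be lost |
| Substance abuse | Possibly, where a disorder already existed; the text does not settle it | May be lost |
| Home safety (e.g. injury) | No | Kept |
| Child protection (abuse, neglect) | No | Kept |

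At most two of the four are exposed.

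**5. Check the other routes to SAE status.** The exception names hospitalisation only. Death, immediate threat to life, persistent disability and important medical events under 9.1 are untouched.

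**6. Size.** Pilot Table 3, in the column for the 81 women with complete data, shows 5 with anxious mood and 3 with a long-term illness. That is at most 5 + 3 = 8 women, fewer if the two overlap. Only 24 of the 81 met the two-factor rule (section 6.2), and the table does not say how many of the 8 were among them. The pilot shows that such conditions occur in the recruiting population. With no admission rates in the protocol, it gives no estimate of affected admissions.

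**The case against.** The strongest reply is that the clause is boilerplate. With no disease under study it has nothing to act on, and the protocol nowhere equates a screening factor such as anxious mood with a disease that progresses. That reading is available, but the sentence stands as an operative rule, and nothing tells an investigator to ignore it.

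Second, an express exception does not strictly contradict the rule it modifies. The stable-condition rule decides whether something is an adverse event, while the exception decides only whether it is serious. This stands. The defect is an undefined exception that works against the purpose of 9.1, not a logical contradiction.

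Third, little information is lost. All adverse events are recorded and followed, and section 9.3 has participants asked about hospitalisation at every study visit. This also stands. A reader might infer that such admissions go unreported; the protocol supports only the loss of SAE status and of the expedited report.

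Fourth, the protocol describes no comparison of SAE counts between arms, so no planned result is shown to be biased. This is fair: the consequence is for oversight and consistent classification, not for an efficacy conclusion.

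Finally, a reader might add the three health-related counts in Table 3 (24 + 5 + 3 = 32) and infer that a large share of the 800 women carry an exempted condition. The table does not support this. It counts criteria rather than women, covers all 81 linked pilot women rather than the eligible ones, and 24 of the 32 are the general-health rating that includes good health.

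**Conclusion.** The point holds in a limited form. Section 9.2 contains an SAE exception with no defined referent. Followed as written, it can take SAE status and the 24-72 hour HREC report away from admissions for worsening of a condition the woman already had, in particular anxious mood or a long-term illness. This rests on one assumption: that an investigator treats such worsening as disease progression, which the wording permits but does not compel.

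A reader might infer that the clause removes most of the risks the protocol expects, or that women in general are enrolled because they are ill. Neither follows, given the two-of-four reach and the seven non-health entry factors. The number of admissions affected is unknown. The change is still worth making, because the rule can misclassify events of a kind the protocol itself expects and is cheap to remove.

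**What to change.** Delete the disease-progression exception from section 9.2, so that seriousness is judged by section 9.1 alone. Reconcile the two sections by stating that hospitalisation for deterioration of a condition present at screening is classified under 9.1. No substitute exception is needed to repair the defect.

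The cost is one sentence in an amendment, approved by the HREC under section 12.3, and somewhat more SAE forms for investigators and the HREC. Eligibility, outcomes, sample size and analysis do not change.

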### **9.3 Eliciting Adverse Event Information**

Adverse events will be recorded from the time the patient signs the informed consent form until 30 days after the last intervention nurse visit. At every study visit patients will be asked “How have you felt since your last visit?” in order to elicit any medically related changes in their well-being. They will also be asked if they have been hospitalised, had any accidents, used any new medication or changed concomitant medication regimens. In addition, AEs will be documented from physical examination findings, clinically significant lab results or other documents (including patient diaries and correspondence from their primary care physician) that are relevant to patient safety.

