- b) Postnatal Learning to Communicate program consisting of 12 monthly sessions commencing when the baby is one month old and finishing when the baby is 12 months old, which include information and activities for parents to encourage child development. Sessions 1-5 are delivered individually during the home visits. Sessions 6-12 are delivered in a group environment. The effectiveness of the Learning to Communicate program has been demonstrated in an unpublished controlled trial, and is a published clinical resource used by clinicians throughout Australasia.

- c) Access to early childhood health services, volunteer home visiting services and family support services.
- d) Group activities and community links including parenting group and walking group specifically for intervention families, and linking into community activities.

The intervention incorporates the standard Key Age and Stage (KAS) visits described in the Service Design Concept above. Existing MECOSH nurse visit checklists (see examples in Manual in **Appendix 5**) will be modified to include statements regarding the need to do KAS at the appropriate times.

**Usual care (control) group:** The control group receive the usual care; that is:

- a) Antenatal care according to MCH protocols, which include:
  - One postnatal home visit by a nurse from the regular child and family nursing service (within 2 weeks of baby's birth)
  - Additional postnatal home or clinic visits with the regular child and family nursing service as indicated by protocols in usual care.
- b) Volunteer home visiting services and family support services within the postcode area as available

Being in the right@home study (both control & intervention) will not preclude access to other support services, except for being part of the Cradle to Kinder (CtK) programs (see Exclusion Criteria, Section 6.2).

Hence the key differences between the right@home intervention and usual care are:

- Home visiting commencing antenatally;
- Continuity of care by the same nurse throughout the 2½ year program;
- Care by nurses with additional training in the right@home and MECOSH program model;
- Standardised postnatal home visiting program to the child's second birthday;
- More frequent, sustained and responsive visits in right@home
- Dedicated social care practitioner;
- Learning to Communicate program and specialised toolkit of focus modules;
- Group activities and proactive links to community activities.

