### **6.2.2 Exclusion Criteria**

Women will be excluded if:

- Their child is removed from the home during the course of the research such that they are ineligible for the trial. If it emerges that child is being removed from his/her home (i.e. intervention nurses inform the study team, or a researcher phone call to the mother to schedule an assessment reveals it), then the CIs [name] and [name] will consider whether the family can remain in the trial on a case-by-case basis. Remaining in the trial will depend on the length of time the child is removed from the home, as it is not possible to assess the effectiveness of an intervention if the family has no access to the intervention or usual care alternative. In some cases, it will only be possible to consider full exclusion of a family at the end of the trial.
- They are enrolled in the Victorian Department of Human Services 'Cradle to Kinder' research program
- They are enrolled in the Tasmanian Department of Health and Human Services CU@home home visiting program
- Do not comprehend the recruitment invitation (e.g. have an intellectual disability such that they are unable to consent to entering the study, or have insufficient English to complete face-to-face assessments, i.e. require an interpreter)
- Have no mechanism for contact (landline or mobile telephone, or email address)
- Experience a critical event such as miscarriage, late termination of pregnancy, stillbirth and neonatal death.

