#### **6.6 Subject Withdrawal**

##### **6.6.1 Reasons for withdrawal**

The research team may withdraw a participant from the study treatment and follow-up procedures if the participant:

- Is in violation of the protocol
- Experiences a serious or intolerable adverse event
- Develops, during the course of the study, symptoms or conditions listed in the exclusion criteria
- Requires early discontinuation for any reason
- Experiences a critical event such as miscarriage, late termination of pregnancy, stillbirth and neonatal death.

The latter will be identified via the research phone calls made throughout the study. We understand that it may be extremely difficult for women to share this information, so phone calls will be

conducted using the same sensitive procedure employed in other studies conducted at the MCRI. The researcher will begin the conversation by asking the mother how she is, which allows the mother to volunteer the information. For mothers in the intervention arm, intervention nurses are likely to learn of these events before the researcher. Intervention nurses will then pass this information back to the research CIs, and one of the CIs will contact the parent to express their sadness, take them off the database, and offer the maternal and child health service number in case parents want additional support. For control participants, the researcher conducting the phone call (CI [name] or RO [name]) will offer the same information, and ask whether the mother would like CI [name] to contact their maternal and child health nurse to request more support.

At enrolment, women will be given study details on the PIS&C, and invited to contact the study team with any details they think we should know about. These processes have worked well in other MCRI studies.

The research team will withdraw all participants from the study treatment if the study is terminated. Patients are free to withdraw from the study at any time upon their request or the request of their legally acceptable representative.

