## **6.8 Continuation of Therapy**

The home visiting intervention will not be offered to participants beyond the child's second birthday.

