### **9.4 Serious Adverse Event Reporting**

#### **9.4.1 SAEs**

Any SAE occurring in a study participant will be reported to the RCH HREC within 24-72 hours of occurrence, in accordance with the safety reporting policy of the HREC. The HREC safety reporting form will be completed, signed and submitted by an investigator.

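### The adverse-event window has no defined end for controls and depends on attendance in the intervention arm, and the handling of pregnancy loss and neonatal death conflicts with the safety and intention-to-treat sections

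*Protocol*

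**What the plan says.** **Window.** Section 9.3 starts the recording of adverse events when the consent form is signed and continues it "until 30 days after the last intervention nurse visit". No other end point is given for either arm. In section 5.1.1 the control arm's nurse contact is usual care: "One postnatal home visit by a nurse from the regular child and family nursing service", with further visits by that service as its protocols indicate. Section 6.8 sets the latest possible intervention visit: "The home visiting intervention will not be offered to participants beyond the child's second birthday". Section 6.6.2 asks mothers who leave the program to remain in the research assessments. Section 7 schedules those for both arms at 6 weeks, 6 months and 18 months by phone, and at 12 and 24 months in person.

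**Critical events.** Section 6.2.2 lists as an exclusion: "Experience a critical event such as miscarriage, late termination of pregnancy, stillbirth and neonatal death". Section 6.6.1 repeats these events as a reason for withdrawal. When an intervention nurse reports one, an investigator is to contact the parent, "express their sadness, take them off the database", and offer a support number. For controls the same support information is offered, but database removal is not stated.

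**Safety and analysis rules.** Section 9.1 counts an adverse event resulting in death as serious, and also lists congenital anomaly. Section 9.2 requires all adverse events to be described on the study database, with death as one outcome category. Section 10.2 compares mothers and children as randomised, whether or not they withdrew. Section 9.4.1 says any SAE "will be reported to the RCH HREC within 24-72 hours of occurrence", in line with the ethics committee's safety reporting policy.

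**The concern.** A comparison of harms needs both arms to be observed over the same period by the same means. Here the period is defined by an event that only one arm can have. Within that arm it is shorter for less engaged mothers, who may well differ in risk. An analysis plan cannot recover events that were never recorded.

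The second part concerns events that occur after randomisation. Handling them as exclusions, and removing the woman from a database, puts at risk the record of the gravest outcomes in a trial that starts in pregnancy. It also departs from the intention-to-treat population that the protocol adopts.

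**Working it through.** The plan gives no figure on this point, so the check sets the sections side by side and adds one line of date arithmetic.

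**Step 1: end of the window by arm.**
- *Control:* section 9.3 refers to an intervention nurse visit, and section 5.1.1 gives controls none. The end is undefined.
- *Intervention:* let s be the child's age in months at the last intervention visit. Taking 30 days as 1 month, the window ends at s + 1. The final assessment is at 24 months (section 7), so the research follow-up outside the window is 24 − (s + 1) = 23 − s months.

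| Last visit, child age s (illustrative) | Window ends | Follow-up outside window | Scheduled contacts outside window |
|---|---|---|---|
| 6 months | 7 months | 17 months | 12, 18, 24 months |
| 12 months | 13 months | 11 months | 18, 24 months |
| 18 months | 19 months | 5 months | 24 months |
| 24 months (latest, section 6.8) | 25 months | none | none |

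The values of s are examples; the protocol gives no distribution of stopping ages. Early stopping is foreseen, though: section 5.2 defines non-compliance as 6 months without attendance, and section 6.6.2 provides for mothers who leave the program and stay in the assessments.

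**Step 2: critical events.**
- Sections 6.2.2 and 6.6.1 make them exclusions and reasons for withdrawal. Section 10.2 keeps mothers in the comparison despite withdrawal. The two do not agree for events after randomisation.
- Section 6.6.1 has nurse-reported cases taken off the database. Section 9.2 wants every adverse event, with its outcome, on the study database. Unless 6.6.1 means something narrower, both cannot be followed.
- Section 11.2 describes a single electronic database for participant details, and also a separate file linking identities to ID codes. It does not settle which one 6.6.1 means.

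**Step 3: route of ascertainment.** Section 6.6.1 expects intervention nurses to hear of these events before the researchers do. Controls depend on the research calls. Reporting routes therefore differ by arm even where the window does not.

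**Step 4: SAE clock (minor).** The scheduled contacts in section 7 are 6 weeks, then 6, 12, 18 and 24 months. From 6 months on they are 6 months apart. An event first disclosed at such a contact can already be well past a limit of 72 hours from occurrence.

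**The case against.** The strongest reply is that much of the collection does not depend on arm. Section 9.3 itself has adverse-event questions at every study visit. Section 9.1 adds a harm question for all women at the 6-week, 6-month and 18-month calls. Section 9.4.1 covers an SAE in any participant. This stands, and it rules out a reading that a reader might otherwise reach, namely that harms cannot be compared by arm at all. It does not remove the defect: the end rule still governs what is recorded, and women taken out of the study do not reach the later contacts.

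A second reply is that the database instruction describes a bereavement call and may mean only a contact list. That is plausible. A reader might infer that these events would be deleted from the data in both arms, but the protocol does not say so. Removal is explicit only for nurse-reported intervention cases, and its scope is undefined. The ambiguity is itself what needs resolving.

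Third, section 9.1 defines an adverse event as occurring in an enrolled participant, and those enrolled are pregnant women. Whether a fetal or infant death counts is not spelled out, though listing congenital anomaly suggests that offspring outcomes are covered. Nor can the listed secondary outcome of pregnancy outcomes carry the argument: the examples in Table 2 are breastfeeding and immunisation.

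Fourth, the size cannot be estimated. The protocol plans for 60% retention, and section 10.1 reports two-year participation of 45% in controls against 57% in the intervention arm of the predecessor trial. Actual observation time could therefore be shorter in controls. This also stands, so no overall loss of person-time or count of lost events is claimed.

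Fifth, the ethics committee's reporting policy is not shown and may already define the clock. The SAE timing is therefore only a minor point.

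**Conclusion.** The concern holds in this form: section 9.3 gives controls no end to adverse-event recording and ties the end to attendance in the intervention arm. The handling of critical events in 6.2.2 and 6.6.1 conflicts with 9.1, 9.2 and 10.2. Followed literally, harm counts by arm would be incomplete and not on a comparable basis. The shared research contacts mean that a valid comparison is still within reach once the wording is repaired.

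The individual shortfall is 23 − s months, which is 17 months for a mother stopping at child age 6 months. This assumes that the end rule is applied as written and that she stays in the research assessments. The trial-wide effect depends on stopping rates, event rates and retention by arm, which the protocol does not give. Confidence is high that the window is badly defined. It is lower on the database instruction, whose meaning is open.

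**What to change.** 1. **Section 9.3:** define one recording window for both arms, from consent to the 24-month assessment, elicited at the same scheduled research contacts. List nurse-reported events separately, because only one arm has that route.
2. **Sections 6.2.2, 6.6.1, 9.2 and 10.2:** reconcile these so that a critical event after randomisation is not an exclusion, and the randomised record and coded event are kept by arm. State that the database instruction refers to the contact list only. This concerns data handling; contact and care after such an event are for the trial team to decide.
3. **Section 9.4.1 (minor):** reconcile the reporting clock with research contacts that are months apart, for example by timing the report from investigator awareness, subject to the ethics committee's policy.

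**Cost:** a wording amendment, using contacts already scheduled. Recording is longer for mothers who leave the program early, up to about 17 months for one who stops at child age 6 months. For a mother visited up to the second birthday, the window closes about 1 month sooner than now (24 against 25 months).
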